#### Objective 3: Determine the Students’ Acceptance of GEN to Improve the Platform as a Learning Tool

At the end of the study, the students will fill out a survey [35] on their experience with the GEN platform as a learning tool (Textbox 2). This survey is anonymous.

Survey to evaluate the students’ acceptance of GEN.1. In this study, there were four experimental groups, and you were enrolled randomly to one of these four groups. Based on your experiences and interactions within GEN, which group do you think you were enrolled in?     a. Group 1. Control     b. Group 2. Self-learning     c. Group 3. Peer-learning     d. Group 4. Peer-learning with expert feedback2. Please rate the level of agreement with the following statements, where 1 means “strongly disagree,” 2 means “disagree,” 3 means “neutral,” 4 means “agree,” and 5 means “strongly agree.”     a. I found GEN to be a user-friendly platform.     b. I found GEN to be a useful platform for improving my suturing skills.     c. I would recommend GEN to other medical students.3. Based on your recent experience, please provide a very brief description of features of GEN that you think we should:     a. Stop (one feature that we should eliminate)     b. Start (one feature that we should add)     c. Change (one feature that works but could be improved upon)     d. Continue (one feature that we should retain and not change)Questions 4 to 12 are derived from the System Usability Scale [35]. The scale ranges from 1 to 5.4. Please rate the level of agreement with the following statements, where 1 means “strongly disagree,” 2 means “disagree,” 3 means “neutral,” 4 means “agree,” and 5 means “strongly agree.”     a. I would like to use GEN frequently.     b. I found GEN unnecessarily complex.     c. I thought GEN was easy to use.     d. I would need the support of a technical person to be able to use GEN.     e. I found the various functions in GEN were well integrated.     f. I thought there was too much inconsistency in GEN.     g. I would imagine that most people would learn to use GEN very quickly.     h. I found GEN very cumbersome (awkward) to use.     i. I felt very confident using GEN.     j. I needed to learn a lot of things before I could get going with GEN.5. During the study, did you access any external resources to help you with the material on GEN?     a. Yes (if yes, please answer question 6)     b. No (If no, you are finished with the survey))6. If you did indeed access external material, please list these resources below.

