## Methods

### Study Design

This will be a prospective randomized controlled study with blinding of expert examiners. The study has been registered (ClinicalTrials.gov NCT04425499).

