### Participant Recruitment

All students in their first year of medical school will receive an email inviting them to participate in the study. If they agree, they will be required to complete a consent form and provide a mailing address (Qualtrics XM).

All students enrolled in this study will be asked to participate using a personal computer. Students will be advised that participation will require their availability for one to three hours on three consecutive days. They will be advised not to study, practice, or view any external videos pertaining to suturing skills for the duration of the study.

When the students agree to participate, they will receive an email with the GEN platform link.

Students' previous experience with suturing will be surveyed, as well as the context of this experience (eg, workshop, former profession).

Upon creation of a new user account on GEN, students will be automatically randomized to one of the four groups and will only have access to the platform set for their study group.

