### Statistical Analysis Plan

First, we will perform descriptive statistical analyses to assess the distributions of the variables of interest and determine the appropriate tests to use as well as the need for a potential transformation. Continuous variables with an asymmetric distribution will be described using median (IQR). Categorical variables will be described with proportions. The remaining variables will be described with mean (SD).

In the following paragraphs, we describe our statistical plan assuming a Gaussian distribution.

Objective 1: We will perform balanced one-way ANOVA to compare mean GRS and Subcuticular Suture Checklist scores among all four groups. First, distinct analyses of the pretest and the posttest scores will be performed. Then, the mean difference between the pretest and the posttest scores will be compared using paired *t* tests if the difference between paired values is consistent.

Objective 2: We will perform balanced one-way ANOVA to compare the performance of students in executing a running subcuticular suture as assessed by the GRS and the Subcuticular Suture Checklist.

Objective 3: We will perform descriptive statistical analyses and correlate the study groups with the Likert scales using the Kruskal-Wallis equality-of-population rank test.

Analysis will be performed in RStudio version 1.2.5033 (RStudio Team) [36] and GraphPad Prism version 8.0.0 for Mac OS X (GraphPad Software) [37]. For each analysis, confidence intervals will be calculated for a 95% confidence level. Statistical hypothesis testing will be performed with an alpha threshold of .05.

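### The acceptance survey names the four arms and asks students to guess theirs before they rate GEN, which adds an avoidable cue to the between-arm comparison in Objective 3

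*Protocol article*

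**What the plan says.** Textbox 2 of the protocol article, under Objective 3, prints the survey in order. Item 1 tells the student "In this study, there were four experimental groups, and you were enrolled randomly to one of these four groups", lists the arms from "Group 1. Control" to "Group 4. Peer-learning with expert feedback", and asks "Based on your experiences and interactions within GEN, which group do you think you were enrolled in".

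Everything the student rates comes later: three agreement items (2a-c), among them "I found GEN to be a useful platform for improving my suturing skills", then a free-text item on features (item 3), then the ten System Usability Scale statements printed as 4a-j. Item 5 asks about external resources and ends the survey for those who answer no.

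For Objective 3, the Statistical Analysis Plan section gives descriptive statistics and says the authors will "correlate the study groups with the Likert scales using the Kruskal-Wallis equality-of-population rank test", with an alpha of .05.

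Two further statements bear on the point. The Study Design section describes a "prospective randomized controlled study with blinding of expert examiners" and does not claim that participants are blinded. Under Participant Recruitment, each student "will only have access to the platform set for their study group". The article gives no reason for placing the guess first.

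**The concern.** Item 1 does two things just before the ratings. It sets out what the other arms received, and it makes the student commit to a view of their own place among them. A student who decides they were the control is then asked whether the platform was useful. So is a student who decides they had the expert.

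A prompt that moved all ratings equally would cancel in a comparison between arms. This one need not, because the label a student is likely to choose depends on the arm they were in. The platform keeps the arms apart during the study, so the survey may be the first time the contrast is put in front of them.

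What is at stake is the reading of Objective 3. Part of a difference in acceptance between arms could be a reaction to the label rather than to the experience of GEN. The GRS and checklist outcomes of Objectives 1 and 2 do not come from this survey and are not touched.

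**Working it through.** The plan states no figure on this point, so there is none to reproduce. The first part of the check is a reading of the order; the second is an illustration.

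**Order.**
1. Item 1 discloses the arms and asks for a guess.
2. Items 2a-c and 4a-j are subjective 1-to-5 ratings and come after it.
3. The Likert ratings are compared across study groups by Kruskal-Wallis.
4. The guess is therefore fixed ahead of an outcome that is tested between arms.

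**Who can be cued.** Groups 3 and 4 have direct contact with peers, and group 4 also with someone labelled as the expert, so they know the main feature of their own arm without item 1. Groups 1 and 2 both learn alone. They differ in whether the pretest and posttest videos contain errors, and neither sees the other's platform. A solitary learner thus has little basis for choosing Control over Self-learning, and any reaction to the Control label is likely to be spread over both groups.

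**Effect of the dilution, by arithmetic.** Let students who pick Control lower a rating by d.
- All of group 1 and none of group 2 react: the arm means shift by (−d, 0, 0, 0) and the overall mean by −d/4. The sum of squared deviations is (3d/4)² + 3(d/4)² = 0.75d².
- Half of groups 1 and 2 react: the arm means shift by (−d/2, −d/2, 0, 0) and the overall mean by −d/4. The sum is 4(d/4)² = 0.25d².

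The spread between arms that the test can pick up is one third as large (0.25/0.75) in the second case.

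**Illustrative rejection rates.** From the plan: four arms of 15, alpha .05. Assumed: a normal rating with mean 3.5 or 3.7 and SD 1, rounded and clipped to 1-5; no true difference between arms; the size of d. The figures are the proportion of simulated trials with Kruskal-Wallis p < .05 on one item (5,000 runs per case; the standard error is at most about 0.7 percentage points).

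| Assumed reaction | All of group 1, none of group 2 | Half of groups 1 and 2 |
|---|---|---|
| None | about 4-5% | about 4-5% |
| Drop of 0.25 | about 8% | about 6% |
| Drop of 0.5 | about 20-21% | about 9-10% |
| Drop of 0.25, group 4 up 0.25 | about 15% | about 12% |
| Drop of 0.5, group 4 up 0.25 | about 31-32% | about 18-20% |

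The two assumed means give nearly the same rates.

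**The case against.** The strongest reply is that the simulated rates are circular. A shift between arms is put in, and the test finds it. The rates are the power of Kruskal-Wallis against an invented shift and do not show that question order produces one. That stands.

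A second reply is that item 1 may reveal little. No participant blinding is claimed, groups 3 and 4 experience their condition directly, and the consent form, which is not shown, may already describe the arms. That also stands as a limit on size. It does not justify the order, because asking for the guess first still brings the contrast to mind at the moment of rating.

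A third reply is that the consequence is modest. Objective 3 serves to improve the platform, its analysis begins descriptively, and several usability statements concern the interface and need not respond to an arm label. The arms also differ in real features, so equal ratings are not the natural expectation. All of this is fair and keeps the point minor.

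A reader might infer more than the text supports in two ways:
- That the acceptance results will be biased, with false-positive rates of 20-30%. The documents give no size for the cue, and those rates need the whole of group 1 and nobody in group 2 to react, when the two groups are hard for their members to tell apart.
- That, because the survey is anonymous and held in Qualtrics, the answer to item 1 will serve as the group variable. The article does not say how the allocated arm is attached to a response, so this cannot be concluded. It is also a separate matter that reordering would not address.

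**Conclusion.** The point holds as a minor design weakness. The printed order places an arm-naming guess before subjective ratings that are then compared between arms, and nothing in the article requires it to come first.

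The size is unknown. On the assumptions above, with a drop of 0.25 to 0.5 point among those who pick Control and no other reaction, one item reaches p < .05 in about 6-9% of trials if half of groups 1 and 2 pick that label. The range is 8-21% if the reaction is confined to the whole of group 1. With no cue it is about 4-5%. The first range fits the design better. If the consent form already sets out the arms, the effect may be smaller still.

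The finding concerns the secondary Objective 3 only. It does not show that the ratings are biased and has no bearing on the primary outcome.

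**What to change.** Move item 1, with its wording unchanged, to after the usability statements (item 4) and before item 5. It should not go to the very end, because item 5 closes the survey for students who report no external resources and they would never reach it. Set the online form so that earlier answers cannot be reopened once the arms have been shown.

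The guess still works as a check on perceived allocation, and the free-text item on features also then comes before the list of arms. The change removes the cue that the survey adds. It cannot remove what students know from peer or expert contact, or from the consent form.

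The cost is one reordering and one setting in an online form. The article reports that no participants had yet been recruited, so no data are affected.

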
#### Objective 4: Develop an Innovative Web-Based Training and Teaching Method to Better Prepare Students for Simulation Training and Clerkship

The GEN platform was built by the research group of [name] at Ontario Tech University. In collaboration with this research group, the platform will be further developed for our study. Each study group will have its own sector on the platform. Therefore, students from one group will not have access to the comments and web-based activity of the other groups. The pretest and the posttest performed in objective 1 will be on GEN, as will the videos uploaded by students in objective 2.

### Materials

Students will require a computer with internet access and a camera.

The pretest and posttest videos will be recorded beforehand using synthetic suture pads and the following instruments: a needle holder, a sterile suture, forceps, and latex gloves.

All students will receive a suturing kit by mail composed of a synthetic suture pad, a needle holder, a sterile suture (3-0 Vicryl), forceps, and latex gloves.

### Sample Size

The experiment is designed so that each of the four groups will have the same sample size. We calculated the sample size based on our primary objective considering a balanced one-way analysis of variance (ANOVA) model. We used the GRS for the calculation.

In the study by Denadai et al [8], subcuticular sutures were assessed using the GRS among three intervention groups. The difference between the lowest mean and the highest mean was 12.25. In that study, we approximated the mean standard deviation within groups to be 1.45. We chose to set the effect size at 0.8 because we do not know the overall standard deviation for all participants. We set the power to 80% and the significance level to 0.05.

Using RStudio, we obtained a sample size of 13 participants per group and a total sample size of 52. We will include 15 participants in each group (total N=60) to have sufficient statistical power. We will invite the whole cohort of first-year medical students (n=300) and enroll the first 60 students who reply favorably.

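### The stated sample-size inputs (four-group ANOVA, effect size 0.8, 80% power, alpha 0.05) do not give 13 per group, and the effect-size metric is not named

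*Protocol article*

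**What the plan says.** The calculation is in the Sample Size section of the protocol article. The model is fixed: "We calculated the sample size based on our primary objective considering a balanced one-way analysis of variance (ANOVA) model". So is the number of arms: "The experiment is designed so that each of the four groups will have the same sample size". The outcome scale is the Global Rating Scale: "We used the GRS for the calculation".

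From an earlier three-group study, the section takes a range of means ("The difference between the lowest mean and the highest mean was 12.25") and a within-group spread ("we approximated the mean standard deviation within groups to be 1.45"). It does not say that either figure entered the calculation. It then gives the effect size and a reason for it: "We chose to set the effect size at 0.8 because we do not know the overall standard deviation for all participants". The error rates follow: "We set the power to 80% and the significance level to 0.05". The result is "Using RStudio, we obtained a sample size of 13 participants per group and a total sample size of 52", and enrolment is set at 15 per group, 60 in total.

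The article's Statistical Analysis Plan section applies the same model to Objective 1, a one-way ANOVA across all four groups.

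**The concern.** The section gives the number of groups, the test, an effect size, the power and the significance level. If the effect size is Cohen's f, nothing else is needed and the result can be checked directly. If it is a standardised difference between arms, only the pattern of means is open, and that can be bracketed. So this is not a request for detail that an article may leave out: inputs and output are both printed, and they disagree.

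This paragraph is the only justification for N = 60 and for the power of the primary analysis. If 0.8 and 13 do not belong together, a reader cannot tell what effect the trial has 80% power for, and so cannot judge what a null result would mean.

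**Working it through.** **Inputs (Sample Size section).** k = 4 equal groups; alpha = 0.05; target power 0.80; effect size 0.8, metric not named; within-group SD 1.45 and range of means 12.25 from the earlier study; planned n = 15 per group.

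**Formula.** For a balanced one-way ANOVA, power is the probability that a noncentral F with k − 1 and k(n − 1) degrees of freedom and noncentrality λ = k·n·f² exceeds the central F critical value. Here f is the root-mean-square deviation of the group means divided by the within-group SD. If d is the largest difference between means in SD units, then for k = 4 f lies between d·√(1/8) (other means at the midpoint) and d/2 (two means at each extreme).

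**Step 1: 0.8 as Cohen's f.** The solution is n = 5.34, so 6 per group and 24 in total. With n = 6, λ = 4 × 6 × 0.64 = 15.36 and power is 85.9%; with n = 5, power is 76.2%. At n = 15, λ = 60 × 0.64 = 38.4 and power is 99.97%.

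**Step 2: 0.8 as the largest standardised difference.**

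| Pattern of means | f | n per group | Power at 13 | Power at 15 |
|---|---|---|---|---|
| Others at midpoint | 0.283 | 35.06 → 36 | 34.5% | 39.8% |
| Equally spaced | 0.298 | 31.66 → 32 | 38.0% | 43.9% |
| One arm apart | 0.346 | 23.71 → 24 | 50.0% | 57.0% |
| Two at each extreme | 0.400 | 18.04 → 19 | 63.4% | 70.9% |

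The totals run from 76 (4 × 19) to 144 (4 × 36). Neither step gives 13.

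**Step 3: what 13 implies.** A four-group ANOVA with n = 13 and 80% power requires f = 0.477.

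**Step 4: routes that reach 13.** Among the readings tried at 80% power and alpha 0.05, two reach it.

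- *Raw-scale reading.* Take 0.8 as the SD of the four group means in GRS points (divisor k − 1, variance 0.64) and 1.45 as the within-group SD (variance 2.1025). Then f = √(0.75 × 0.64 / 2.1025) = 0.478 and n = 12.96, so 13. Power is 80.2% at 13 and 86.4% at 15. The standardised effect is then about 0.48, not 0.8.
- *Two-arm total spread over four arms.* A two-sided two-sample t test at d = 0.8 needs 25.52, so 26 per arm: 2 × 26 = 52 and 52 / 4 = 13. This is not an ANOVA calculation.

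**Step 5: what 15 per group delivers.** Eighty per cent power is reached at f = 0.4415. The matching largest difference is 2 × 0.4415 = 0.88 SD with two means at each extreme, and 0.4415 × √8 = 1.25 SD with the others at the midpoint.

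**The case against.** A reader might infer that the trial is underpowered. The document does not support that. It never says that 0.8 is a difference between arms in SD units. The conventional effect size for an ANOVA is f, and at f = 0.8 the trial is larger than it needs to be. The raw-scale route uses two numbers printed in the section, stays within a four-group ANOVA, reaches 13, and leaves 86% power at 15 per group. This objection stands: the plausible readings run from about 40% to over 99.9% power, so no shortfall is shown.

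The raw-scale route does not rescue the paragraph, however. It makes the label of 0.8 wrong, it needs the k − 1 divisor (f = 0.8 / 1.45 = 0.55 would give 10 per group), and it fits poorly with the reason given for choosing 0.8.

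A reader might also take 0.88 to 1.25 SD as a threshold below which nothing is detected. It is only the difference at which power reaches 80%. Even if 0.8 is a standardised difference, the test would find it 40% to 71% of the time.

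The earlier study's range of 12.25 with SD 1.45 is about 8.4 SD, far above any effect discussed here. Those data concern suture execution, so they establish nothing about power for rating videos. Equally, nothing in the article shows that a difference of 0.88 to 1.25 SD is too coarse a target.

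Finally, the remark about the overall SD might mean the unknown variability among this trial's own participants. That is possible, but the wording does not say so.

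**Conclusion.** The concern holds as a failure to reproduce. With the metric unnamed, the stated inputs give 6 per group on one standard reading and 19 to 36 on the other, so 13 is out by a factor of about 2 in one direction (13 / 6) or 1.5 to 2.8 in the other (19 / 13 and 36 / 13). Rounding cannot explain that. Under either route that reaches 13, the text needs correcting: in one the effect-size label is wrong, in the other the method is. Which of them occurred cannot be settled from the article.

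The figures assume the omnibus F test, normal outcomes, a common within-group SD and 15 analysed participants in every group.

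Two side points do not bear on the arithmetic. First, one-way ANOVA power uses the within-group SD, so not knowing an overall SD is not, as worded, a reason for choosing 0.8. Second, the calculation is said to serve the primary objective, which is rating videos (Objective 1), whereas the Introduction describes the earlier study as one of suture execution, which is the Objective 2 outcome.

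**What to change.** Keep N = 60 and rewrite the paragraph:

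- Name the effect-size metric, the SD used and the R call, then correct the effect-size label or the calculated sample size, whichever does not match.
- State what the planned size delivers: 15 per group gives 80% power at f = 0.44 in the four-group ANOVA, a largest difference of about 0.88 to 1.25 within-group SD depending on the pattern of means.
- If 0.8 was meant as a standardised difference between arms, report the 40% to 71% power at 15 per group instead of 80%.
- Replace the reason based on the overall SD.
- Note that the cited GRS data come from suture execution and not from the primary video-rating outcome.

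The cost is one reworded paragraph and possibly a less favourable stated detectable effect. No extra participants are needed and the design is unchanged. The abstract reports that nobody had yet been recruited, so on that account the correction can precede any data.

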### Ethics

This study will be conducted following the Declaration of Helsinki on human research. The protocol has been approved by our institutional review board (CERSES 20-068-D). Any amendment to the protocol must be approved by this committee. A consent form will be sent to the students. Participation in this study is voluntary. Students will not be exposed to any risks apart from those inherent in the manipulation of sterile needles. This small risk will be mentioned in the consent form and is considered to be low compared to the benefits of the study.

Students’ anonymity will be maintained on the GEN platform throughout the study.

